## Abstract

**Background:**

Standard therapy for Glioblastoma multiforme (GBM) involves maximal safe tumor resection followed with radiotherapy and concurrent adjuvant temozolomide. About 20 to 30% patients undergoing their first post-radiation MRI show increased contrast enhancement which eventually recovers without any new treatment. This phenomenon is referred to as pseudoprogression. Differentiating tumor progression from pseudoprogression is critical for determining tumor treatment, yet this capacity remains a challenge for conventional magnetic resonance imaging (MRI). Thus, a prospective diagnostic trial has been established that utilizes multimodal MRI techniques to detect tumor progression at its early stage. The purpose of this trial is to explore the potential role of intravoxel incoherent motion diffusion-weighted imaging (IVIM-DWI) and three-dimensional arterial spin labeling imaging (3D-ASL) in differentiating true progression from pseudoprogression of GBM. In addition, the diagnostic performance of quantitative parameters obtained from IVIM-DWI and 3D-ASL, including apparent diffusion coefficient (ADC), slow diffusion coefficient (D), fast diffusion coefficient (D*), perfusion fraction (f), and cerebral blood flow (CBF), will be evaluated.

**Methods:**

Patients that recently received a histopathological diagnosis of GBM at our hospital are eligible for enrollment. The patients selected will receive standard concurrent chemoradiotherapy and adjuvant temozolomide after surgery, and then will undergo conventional MRI, IVIM-DWI, 3D-ASL, and contrast-enhanced MRI. The quantitative parameters, ADC, *D*, *D**, *f*, and CBF, will be estimated for newly developed enhanced lesions. Further comparisons will be made with unpaired *t*-tests to evaluate parameter performance in differentiating true progression from pseudoprogression, while receiver-operating characteristic (ROC) analyses will determine the optimal thresholds, as well as sensitivity and specificity. Finally, relationships between these parameters will be assessed with Pearson’s correlation and partial correlation analyses.

**Discussion:**

The results of this study may demonstrate the potential value of using multimodal MRI techniques to differentiate true progression from pseudoprogression in its early stages to help decision making in early intervention and improve the prognosis of GBM.

**Trial registration:**

This study has been registered at ClinicalTrials.gov (NCT02622620) on November 18, 2015 and published on March 28, 2016.

## Highlights

Intravoxel incoherent motion (IVIM) magnetic resonance imaging (MRI) allows the simultaneous acquisition of diffusion and perfusion parameters which reflect tumor cellularity and vascularity, respectively.Arterial spin labeling (ASL) and IVIM are two commonly used perfusion MRI techniques without introducing contrast agents and are considered as safe and reliable methods.

## Background

Glioblastoma multiforme (GBM) is the most common malignant primary brain tumor in adults. A combination of radiation therapy with concurrent or adjuvant temozolomide (TMZ) following maximum safe tumor resection can significantly improve patients’ survival, and is currently the standard treatment for GBM. Even with this standard treatment, the survival of GBM patients remains extremely poor and the overall median survival time is 14–18 months after treatment [1, 2].

GBM treatment efficacy is generally evaluated with contrast-enhanced MRI in conjunction with clinical assessment. Only recently have radiologists and clinicians observed some transient treatment-induced changes after radiotherapy which demonstrate tumor progression features in contrast-enhanced MRI such as progressive enlargement and new enhancement. However, these features mainly derive from postsurgical changes including radiation effects, treatment-induced inflammation, and ischemia [3, 4]. This phenomenon is referred to as pseudoprogression. Chemotherapy with TMZ significantly increased the rate of pseudoprogression [5, 6]. It is reported that half of the patients with high-grade gliomas after chemoradiotherapy showed an enlarged enhancement area on contrast-enhanced T1-weighted magnetic resonance (MR) images, of which 20 to 30% were pseudoprogression [7–9].

While both tumor progression and pseudoprogression exhibit progressive enlargement and new enhancement within a radiation field [3], the treatment and prognosis for them are totally different. Tumor progression reflects treatment failure and the treatment plan should be adjusted accordingly [10], while pseudoprogression is associated with a favorable prognosis and can improve spontaneously with adjuvant TMZ. If the latter is misdiagnosed as true progression, the treatment efficacy can be underestimated, thus leading to the inappropriate adjust of therapy. However, true progression can not be easily differentiated from pseudoprogression with current conventional MRI sequences. Therefore, new imaging tools that can assist clinicians in effectively identifying true progression versus pseudoprogression within 6 months after concurrent chemoradiotherapy are needed, which will facilitate the selection of appropriate treatment or the early termination of an invalid treatment plan.

There have been several studies in which researchers differentiated true progression from treatment effects by using advanced MR imaging techniques, such as diffusion weighted magnetic resonance imaging (DWI) and dynamic susceptibility-weighted contrast-enhanced (DSC) MRI. True progression exhibits significantly lower apparent diffusion coefficient (ADC) values compared with pseudoprogression [11, 12], reflecting the high cellularity of progressed tumor. Considering that ADC values can be compromised by perfusion, Le Bihan et al. introduced an intravoxel incoherent motion (IVIM) technique [13, 14]. Slow diffusion coefficient (D) is the diffusion parameter which reflects the diffusion coefficient for water while fast diffusion coefficient (D*) represents perfusion-related diffusion. Fraction of fast ADC (f) is the perfusion fraction linked to microcirculation which has been successfully applied to glioma grading and to differentiate recurrent tumors from treatment-related changes [15, 16]. DSC is a T2*-weighted technique to measure relative cerebral blood volume (rCBV) and lower mean rCBV values in pseudoprogression was previously used to differentiate from true progression [17]. However, radiotherapy and chemotherapy for GBM destroy blood–brain barrier, allowing gadolinium-based contrast agents to leak into the interstitial fluid, which may lead to the underestimation of rCBV with DSC [18]. Three-dimensional arterial spin labeling (3D-ASL) is another non-invasive and contrast agent-free perfusion imaging method to measure cerebral blood flow (CBF) [19]. The diagnostic performance of 3D-ASL has been found to be equivalent to DSC MRI in assessing brain tumor perfusion, particularly for those patients not suitable for DSC because of renal failure [20].

Despite the application of IVIM and 3D-ASL in glioma study, there still lacks study in which IVIM is combined with 3D-ASL in the same GBM patient cohort to evaluate their efficacy of differentiate true tumor progression from pseudoprogression as a consequnence of radiochemotherapy for GBM.

Therefore, the current prospective diagnostic trial was designed to evaluate the ability of IVIM-DWI and 3D-ASL to distinguish true tumor progression from pseudoprogression in GBM. The diagnostic performance of the quantitative parameters obtained from IVIM-DWI and 3D-ASL will also be compared.

## Methods/Design

This prospective single institution observational study will include two case groups and has been approved by the Ethics Committee of Tangdu Hospital (TDLL-20151013). The scheme of the current trial is presented in Fig. 1.

**Fig. 1 Fig1:**
[figure not shown]
Flowchart of the current prospective diagnostic trial

### Patient Selection

#### Inclusion criteria

Patients that recently received a histopathological diagnosis of GBM from Tangdu Hospital are considered for enrollment in the present study. The criteria for selection are: (1) a recent histopathologic diagnosis of GBM according to criteria of the World Health Organization; (2) total or partial resection of the enhanced tumor component; (3) baseline contrast-enhanced MRI performed within 24 ~ 48 h after surgery; (4) standard radiation therapy with concurrent TMZ and six cycles of adjuvant TMZ after surgery; (5) follow-up IVIM-DWI and 3D-ASL performed on the same 3 T MRI scanner within 6 months after the completion of radiation therapy with concurrent TMZ, when pseudoprogression is prevalent [21], however as a long project, we will follow up glioma patients as long as possible;(6) Without receiving corticosteroid management at 3 days before imaging;(7) the presence of newly developed enhanced lesions or enlarged enhanced lesions within the radiation field; (8) surgical resection of enhanced tissue or adequate clinicoradiologic follow-up to definitively diagnose true progression or pseudoprogression according to Response Assessment in Neuro-Oncology (RANO) criteria [22].

#### Exclusion criteria

Subjects will be excluded based on any of the following conditions: (1) without contrast-enhanced MRI performed within 24 ~ 48 h after surgery; (2) absence of newly developed enhanced lesions or enlarged enhanced lesions after the end of radiation therapy with concurrent TMZ; (3) non-standard treatment after surgery; or (4) patient does not complete clinicoradiologic follow-up or surgical resection of enhanced tissue to definitively diagnose true progression or pseudoprogression.

### IVIM model

DWI dada will be analyzed using the same protocol as described in our previous publication [15]. DWI will be analyzed with an IVIM model (Eq. 1), where *S0* and *S*(*b*) are the signal intensities of attenuation at a *b-*value of 0 s/mm^2^ and at a *b*-value > 0 s/mm^2^, respectively. *D* is the diffusion parameter which reflects the diffusion coefficient for water, *D** represents perfusion-related diffusion and *f* is the perfusion fraction linked to microcirculation.

Considering that D* is significantly larger than D [14, 23]. The contribution of *D** to signal decay can be neglected with a *b*-value > 200 s/mm^2^. Thus, Eq. (1) can then be simplified, and the estimation of D can be obtained by using only b values larger than 200 s/mm^2^, with a simple linear fit Eq. (2), then *D** and *f* will be generated with low *b*-values by using a nonlinear regression algorithm based on Eq. (1).1$$ S(b)/ S 0= f\; exp\left(- b\times D*\right) + \left(1- f\right)\  exp\ \left(- b\times D\right) $$
2$$ S(b)\ / S 0 = exp\ \left(- bD\right) $$

The ADC value will be derived from a monoexponential equation with all *b*-values by Eq. (3).3$$ S(b)\ / S 0 = exp - \left( ADC \times b\right) $$

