### Image acquisition

Upon completion of radiation therapy with concurrent TMZ, follow-up MRI scans will be performed with a 3.0 T MRI system (MR750; GE Healthcare, Milwaukee, WI, USA) with an 8-channel head coil. Conventional MRI, DWI with 13 b-values (0 ~ 1500 s/mm^2^), 3D-ASL, and contrast-enhanced MRI will be arranged in regular sequence for each patient’s first follow-up visit. Conventional MRI sequences will include spin-echo T1-weighted imaging, fast spin-echo T2-weighted imaging, and fluid-attenuated inversion recovery imaging (FLAIR). The IVIM DWI will be performed prior to gadolinium injection with a single-shot diffusion-weighted spin-echo echo-planar sequence using 13 different b-values: 0, 10, 20, 30, 50, 80, 100, 200, 300, 500, 800, 1000, and 1500s/mm^2^. These b-values were selected to cover both initial pseudo diffusion decay (b < 200 s/mm^2^) and molecular diffusion decay (b ≥ 200 s/mm^2^) [24]. In total, 20 axial slices covering the entire brain will be obtained. The following MR imaging parameters will be used: field of view (FOV) = 256 × 256 mm^2^, slice thickness = 5 mm, slice gap = 1.5 mm, repetition time (TR) = 3000 ms, echo time (TE) = minimum, matrix =128 × 128. The total acquisition time will be 5 min and 45 s.

A 3D spiral fast spin echo (FSE) sequence will be used to obtain 3D-ASL perfusion images. The MRI parameters will be: 512 sampling points on eight spiral arms, spatial resolution = 3.64 mm, TR = 4590 ms, TE = 10.5 ms, slice thickness = 4.0 mm, number of slices = 40, FOV = 240 × 240 mm^2^, number of excitations (NEX) = 3.0. The total acquisition time will be 4 min.

Finally, a contrast-enhanced T1-weighted spin echo sequence will be performed in the transverse, sagittal, and coronal planes following a bolus injection of 0.1 mmol/kg of gadodiamide (Omniscan; GE Healthcare, Co. Cork, Ireland).

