### Primary outcome measure

 Differences in diffusion-related parameters between true tumor progression and pseudoprogression according to the different fitting model
*D* and ADC will be derived from biexponential and monoexponential models, respectively. We hypothesized that true tumor progression and pseudoprogression can be distinguished based on these two values and true tumor progression can exhibit significantly lower mean *D* and ADC values compared with pseudoprogression. In addition, we hypothesized that *D*, which separates perfusion effects, will be a more promising parameter in distinguishing true tumor progression from pseudoprogression compared with ADC which can be compromised by perfusion. Differences in perfusion-related parameters between true progression and pseudoprogression Data regarding *D**, *f*, and CBF will be summarized. We hypothesized that *D**, *f*, and CBF will significantly differ between true tumor progression and pseudoprogression and Mean D*, f, and CBF values will be signifcantly lower for pseudoprogression than for true progression. Diagnostic Performance of the IVIM and 3D-ASL Parameters Receiver operating characteristic (ROC) analyses will determine corresponding cutoff points for differentiating true tumor progression from pseudoprogression based on ADC, *D*, *D**, *f*, and CBF values. In addition, sensitivity, specificity, and area under curve (AUC) for identifying true progression will be calculated in each case when pseudoprogression is differentiated. We will make a comparison among all the IVIM and 3D-ASL parameters to identify which has the best sensitivity/specificity with regards to early diagnosis. Establishment of Clinical prediction modelSingle factor analysis will show which covariates affect the judgment of newly developed enhanced or enlarged enhanced lesions, such as age, gender, radiation dose, karnofsky performance score, lesion region and imaging characteristics. A logistic regression equation will be performed to identify those covariates, IVIM and 3D-ASL parameters that contribute to the diagnostic differentiation between true progression and pseudoprogression.

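### Eq. (2) drops the factor (1−f) from Eq. (1); if it is fitted as printed, anchored at the b=0 signal, D is biased upward by perfusion

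*Protocol article*

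**What the plan says.** All of this is in the protocol article.

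- **IVIM model, definitions.** S0 and S(b) "are the signal intensities of attenuation at a *b-*value of 0 s/mm^2" and at b above 0, respectively. Eq. (1) is S(b)/S0 = f exp(−bD\*) + (1−f) exp(−bD).
- **IVIM model, step 1.** The D\* contribution is treated as negligible above b = 200. Then "Eq. (1) can then be simplified, and the estimation of D can be obtained by using only b values larger than 200" s/mm², by a linear fit of Eq. (2), which is printed as S(b)/S0 = exp(−bD). The section does not say whether the line has its own intercept.
- **IVIM model, step 2.** f and D\* are then obtained from Eq. (1) by nonlinear regression on the low b-values. ADC comes from Eq. (3), a single exponential over all b-values.
- **Image acquisition.** The b-values are "0, 10, 20, 30, 50, 80, 100, 200, 300, 500, 800, 1000, and 1500s/mm^2". This section assigns "molecular diffusion decay (b ≥ 200" s/mm²) to the diffusion segment, whereas the IVIM model section uses values strictly above 200.
- **Primary outcome measure.** D and ADC are expected to be lower, and f higher, in true progression. D, "which separates perfusion effects, will be a more promising parameter in distinguishing true tumor progression from pseudoprogression compared with ADC", is the parameter expected to do better.

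**The concern.** Removing the D\* term from Eq. (1) leaves the tissue term with its weight (1−f). Eq. (2) loses that weight while S0 is still defined as the b=0 signal. Eq. (2) then has the same form as the ADC model, Eq. (3), and differs only in the b-values used.

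D is a primary parameter, valued because it is meant to be free of perfusion. If Eq. (2) is fitted as printed, the missing term −ln(1−f) is absorbed into the slope, so D rises with f. The protocol expects true progression to have lower D and higher f, so this bias would work against the expected D difference and against the claim that D outperforms ADC. The second step takes over the same D, so f and D\* would be affected too. f also enters the secondary correlation with CBF.

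**Working it through.** **Inputs from the document.** Eqs. (1) to (3); S0 at b=0; b-values above 200, namely 300, 500, 800, 1000 and 1500 s/mm².

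**Assumed inputs.** The document gives no values of D, D\* or f. I take D = 1.0×10⁻³ for the single-lesion bias, D = 0.9 (true progression) versus 1.1×10⁻³ (pseudoprogression) for the contrast, D\* = 10×10⁻³ mm²/s, and a range of f. Signals are noise-free. The plan states no figure to reproduce.

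**Algebra.** With f exp(−bD\*) neglected, ln[S(b)/S0] = ln(1−f) − bD.

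- *Anchored fit (Eq. (2) read literally).* Least squares through zero at b=0 gives slope = D − ln(1−f) × Σb/Σb².
- *Free intercept.* The slope is D and the intercept absorbs ln(1−f).

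**Bias of the anchored fit.** Σb = 4100 and Σb² = 90,000 + 250,000 + 640,000 + 1,000,000 + 2,250,000 = 4,230,000, so Σb/Σb² = 9.69×10⁻⁴.

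- f = 0.05: 0.0513 × 9.69×10⁻⁴ = 0.050×10⁻³, or 5%
- f = 0.10: 0.1054 × 9.69×10⁻⁴ = 0.102×10⁻³, or 10%
- f = 0.15: 0.1625 × 9.69×10⁻⁴ = 0.158×10⁻³, or 16%

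Generating full Eq. (1) signals at the protocol's b-values and refitting gives 4.9%, 10.1% and 15.6%. A nonlinear fit of Eq. (2) gives 7%, 15% and 24%. A free intercept gives under 1%.

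**Group contrast in D** (true value 0.200, units 10⁻³ mm²/s, from the generated signals):

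| f, true vs pseudoprogression | Anchored | Lost | Free intercept |
|---|---|---|---|
| 0.08 vs 0.08 | 0.200 | 0% | 0.200 |
| 0.06 vs 0.04 | 0.180 | 10% | 0.199 |
| 0.12 vs 0.07 | 0.147 | 27% | 0.198 |
| 0.15 vs 0.05 | 0.093 | 54% | 0.195 |

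The formula agrees. At 0.12 versus 0.07 the biases are 0.124 and 0.070, so the contrast is 0.200 − 0.054 = 0.146.

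**D against ADC.** At 0.12 versus 0.07, an ADC from Eq. (3) fitted through the b=0 signal on all b-values has a contrast of 0.144. The anchored D contrast of 0.147 is almost the same.

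**Second step.** With D fixed at its anchored value, a true f of 0.10 is returned as about 0.072 when b up to 200 is used. With a free-intercept D it is returned as about 0.099.

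**Cut-off.** Adding b = 200 to the high-b set moves the 0.12 versus 0.07 contrast from 0.147 to 0.145 (anchored) and from 0.198 to 0.195 (free intercept).

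**The case against.** The strongest reply is that the text does not say the line passes through the b=0 signal. It says D comes only from b-values above 200 by a linear fit, and anchoring would bring in the b=0 measurement. A straight line through ln S at b = 300 to 1500 with its own intercept suits those words at least as well, and its slope is essentially unbiased whatever f is. The section also defers to the group's earlier publication for the analysis, and Image analysis says the maps are generated automatically on the workstation. The printed equation may therefore be shorthand or a slip rather than the algorithm. This stands: the bias is conditional.

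Two further points stand. The loss of contrast needs f to differ between groups, which the protocol only hypothesises, so the loss starts at zero. The effect on the planned t-test also depends on a between-patient SD that the document does not give. With 50 per group and a contrast of 0.147×10⁻³, power would be 95%, 83% and 68% at assumed SDs of 0.20, 0.25 and 0.30×10⁻³.

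The reply does not rescue the equation. A free intercept is not Eq. (2) with S0 as defined, and nothing in the document says one is used. Eq. (1), in the same section, carries (1−f) intact, so the text-reading process is an unlikely cause.

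**Conclusion.** Eq. (2) is a wrong formula for a primary parameter. It does not follow from Eq. (1) and is correct only at f=0. Fitted as printed, anchored at b=0, it would bias D upward by −ln(1−f) × Σb/Σb², about 5% to 16% for f from 0.05 to 0.15. It would also bias f downward and bring D close to ADC. If f is higher in true progression, it would shrink the D contrast by an amount that depends on the group difference in f: none at equal f, about 10% at 0.06 versus 0.04, and about 27% at 0.12 versus 0.07. The algebra is certain. The sizes rest on assumed D, D\* and f and on noise-free signals.

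A reader might infer that the trial's D values are in fact biased, or that its primary comparison is compromised. The documents do not support that, because the fit actually run is not shown and a free-intercept fit would be almost unaffected. The differing cut-offs at b = 200 are a real but minor inconsistency.

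**What to change.** Replace Eq. (2) with ln S(b) = ln[S0(1−f)] − bD and state that it is fitted with a free intercept over the high-b set. Then fit f and D\* from Eq. (1) with D held at that value. Use one cut-off for the high-b set, either including or excluding b = 200, in both IVIM model and Image acquisition.

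Check that the workstation software fits this form. If it does, only the text changes. If it was anchored at b=0, reprocess the stored images for D, f and D\*. In neither case are new scans or patients needed.

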### Image acquisition

Upon completion of radiation therapy with concurrent TMZ, follow-up MRI scans will be performed with a 3.0 T MRI system (MR750; GE Healthcare, Milwaukee, WI, USA) with an 8-channel head coil. Conventional MRI, DWI with 13 b-values (0 ~ 1500 s/mm^2^), 3D-ASL, and contrast-enhanced MRI will be arranged in regular sequence for each patient’s first follow-up visit. Conventional MRI sequences will include spin-echo T1-weighted imaging, fast spin-echo T2-weighted imaging, and fluid-attenuated inversion recovery imaging (FLAIR). The IVIM DWI will be performed prior to gadolinium injection with a single-shot diffusion-weighted spin-echo echo-planar sequence using 13 different b-values: 0, 10, 20, 30, 50, 80, 100, 200, 300, 500, 800, 1000, and 1500s/mm^2^. These b-values were selected to cover both initial pseudo diffusion decay (b < 200 s/mm^2^) and molecular diffusion decay (b ≥ 200 s/mm^2^) [24]. In total, 20 axial slices covering the entire brain will be obtained. The following MR imaging parameters will be used: field of view (FOV) = 256 × 256 mm^2^, slice thickness = 5 mm, slice gap = 1.5 mm, repetition time (TR) = 3000 ms, echo time (TE) = minimum, matrix =128 × 128. The total acquisition time will be 5 min and 45 s.

A 3D spiral fast spin echo (FSE) sequence will be used to obtain 3D-ASL perfusion images. The MRI parameters will be: 512 sampling points on eight spiral arms, spatial resolution = 3.64 mm, TR = 4590 ms, TE = 10.5 ms, slice thickness = 4.0 mm, number of slices = 40, FOV = 240 × 240 mm^2^, number of excitations (NEX) = 3.0. The total acquisition time will be 4 min.

Finally, a contrast-enhanced T1-weighted spin echo sequence will be performed in the transverse, sagittal, and coronal planes following a bolus injection of 0.1 mmol/kg of gadodiamide (Omniscan; GE Healthcare, Co. Cork, Ireland).

